# Do PROMs or Sensor-Based Monitoring Detect Improvements in Patients’ Knee Function After Total-Knee Arthroplasty?—A Study Protocol for a Prospective Controlled Study

**DOI:** 10.3390/s25010118

**Published:** 2024-12-27

**Keywords:** PROM, TKA, performance-based, knee function, rehabilitation, knee alignment, IMU

## Abstract

Determining whether preoperative performance-based knee function predicts postoperative performance-based knee function and whether patient-reported outcome measures (PROMs) completed by participants can detect these changes could significantly enhance the planning of postoperative rehabilitation for patients following total knee arthroplasty (TKA). This study aims to collect data on performance-based knee function using inertial measurement units (IMUs) worn by participants both preoperatively and postoperatively. PROMs will be completed by the patients before and after surgery to assess their ability to detect the same changes in performance-based knee function measured by the sensors. Additionally, the study will investigate the correlation between the degree of knee alignment correction and postoperative performance-based knee function in participants after TKA.

## 1. Introduction

In knee osteoarthritis (KOA), the cartilage and joint structure deteriorate, leading many patients to report difficulties in performing everyday tasks such as walking, climbing stairs, or kneeling down [1,2]. In later stages of osteoarthritis, as the cartilage is further damaged, patients experience pain even at rest, including while sitting down, or at night [3]. Furthermore, joint mobility and range of motion also suffer as most patients with end stage osteoarthritis exhibit deficits in their ability to perform knee flexion, knee extension movement, or both [4].

It is rather unknown how strong the correlation is between the expression of knee osteoarthritis (Kellgren and Lawrence grading), knee alignment deformity, and performance-based knee function (including general level of activity). Cumulative evidence suggests that combinations of structural and clinical risk factors may be able to predict radiographic knee osteoarthritis progression [5,6]. Kellgren and Lawrence grading is a widely used medical grading system to classify degrees of osteoarthritis on knee X-rays [6,7]. Grades 3 and 4 on the Kellgren and Lawrence scale are considered end-stage, at which point most patients have exhausted conservative treatment options [7,8]. Still patients with Grade 3 or 4 often benefit similarly from knee replacement surgery [9,10,11].

Patients with the symptoms and radiological signs of end-stage knee osteoarthritis are often scheduled for knee arthroplasty, mainly due to increased pain and reduced function following the breakdown of joint tissue and structure [9,12]. Depending on the location of the osteoarthritis and the severity of the symptoms and other aspects like age, either osteotomy, unicompartmental knee arthroplasty, or total knee arthroplasty may be indicated [9,13,14]. The decision-making process regarding the implantation of unicompartmental knee arthroplasty versus total knee arthroplasty involves consideration of multiple additional factors, including patient age, gender, and body mass index (BMI) [15,16].

Total knee arthroplasty is performed when a patient meets specific criteria, including symptoms and radiological signs. Also, robotic and personalized versus standard arthroplasty techniques must be considered [15,16,17,18].

Currently, there are various approaches to describing physical function in patients with knee osteoarthritis after total knee arthroplasty [19,20]. In a previous project, an investigation into how patients’ mobility was during a hospital stay was carried out with the use of new IMUs [21].

During this study, IMUs will primarily be used to track knee movement and produce data to help establish a correlation between the pre- and postoperative performance-based knee function, which will aid in determining if the former is predictive of the latter [19,20,21,22,23]. This information could serve a key role in planning postoperative rehabilitation, as well as in setting appropriate patients’ expectations during the perioperative period [14,17,24]. The expected postoperative performance-based knee function gives caregivers better insights into how to give appropriate attention in the necessary areas in the acute and postacute phase [25,26].

Patient-reported outcome measures (PROMs) are a mainstay in patient-centered medical treatment and have been employed in osteoarthritis for 35 years [27]. They allow patients to provide their own subjective report of how a treatment has affected them [28,29,30]. PROMs have a special role to play in orthopedics, especially in arthroplasty, as patients can report their ability to complete everyday tasks and compare it to their preoperative levels, as well as report on their comfort with their new prosthetic joint [31]. Furthermore, PROMs help clinicians assess the functional and psychological outcomes of surgical interventions, providing a more comprehensive evaluation of treatment success [32]. During the study, it will be of further interest whether participants will report the same degree of improvement that the IMUs identify through their subjective answers across three different PROMs. Through this study, not only will the uniformity and exchangeability of the PROMs be investigated, but their ability to reflect objective measured changes will also be examined.

Osteoarthritis of the knee can often be accompanied by one of two characteristic lower limb alignment pathologies: valgus or varus deformity [33,34]. These deformities tend to produce a more pronounced damage in either the medial or the lateral compartment of the knee [35,36]. The degree of required axis correction during total knee arthroplasty is a hotly debated topic, with mechanical, functional, and kinematic alignments taking different approaches [34,37,38]. This study will investigate the association between the degree of knee alignment correction and the postoperative performance-based knee function will be investigated. This is of interest due to the implications it could have for total knee arthroplasty planning, as surgeons can seek to provide an axis correlation most closely associated with the best performance-based knee function, rather than the previously accepted doctrine. Identifying an optimal alignment strategy may help reduce complications, improve patient satisfaction, and enhance long-term functional outcomes [39,40]. Additionally, understanding the influence of alignment correction on knee biomechanics could further refine personalized surgical approaches for osteoarthritis patients [41].

The primary hypothesis of the planned trial is that participants’ performance-based knee function two weeks pre-operation will predict their performance-based knee function six weeks post operation. The secondary hypothesis is that an improvement in performance-based knee function six weeks after total knee arthroplasty will be observed.

Additionally, it is further hypothesized that an inverse correlation between the extent of leg axis correction and knee function six weeks post operation will be observed.

## 2. Materials and Methods

### 2.1. Participants

From November 2024 till April 2025, 30 patients will be enrolled in the study. A power analysis was conducted to determine that a sample size of 30 patients would be sufficient for the study, based on the hypothesis that participants’ performance-based knee function two weeks pre-operation will predict their performance-based knee function six weeks post operation. The inclusion criteria include meeting the requirements for total knee arthroplasty in the S2k-Criteria [42] from the German Society of Orthopedics and Trauma (DGOU) summarized in Table 1, completing the preoperative examination at the ambulatory facilities of Oberlinklinik Potsdam (Germany), and informed consent to participate in the study. Exclusion criteria will include previous operations changing the knee alignment, such as high tibial osteotomies or distal femur osteotomies in the patient’s past, and comorbidities that decrease the expected knee function or activity level, such as paralysis of the lower limbs, neurological deficits in the lower limbs, and osteoarthritis in other lower limb joints.

This study has been prospectively registered in the German Clinical Trial Registry under the ID number DRKS00033537.

Ethical approval was given by the Ethics Committee of the Brandenburg Medical University (Neuruppin, Brandenburg, Germany) (ref. number: E-02-20230302). All participants will provide written consent.

### 2.2. Inertial Measurement Units

The Orthronic Smart Knee (OSK) sensor is equipped with an inertial measurement unit, incorporating a 3-axis accelerometer, gyroscope, and magnetometer, enabling the recording of knee motion at a sampling rate of 25 Hz. The OSK is equipped with a temperature sensor and an air pressure sensor, both measured at a sampling rate of 1 Hz. The sensor weighs in at 6 g and measured 37 mm × 26 mm × 8 mm (length × width × height).

The IMU can directly transmit data to a tablet via Bluetooth or store measured data in an integrated 512 MB memory bank for later access. During the development phase, the IMU’s reliability was assessed using a 10-camera motion capture system (VI-CON-MX-S, Vicon Motion System Ltd., Oxford, UK) with defined movements. This testing revealed an average deviation of 5 degrees [43].

### 2.3. IMU Application and Measurements

Two IMUs will be taped to the anterior distal thigh, approximately at the level of the quadriceps muscle, and on the proximal anteromedial aspect of the lower leg of each participant, respectively. As seen in Figure 1, the IMUs will be attached with the use of soft silicone adhesive non-woven fabric and cushioned from the skin with non-woven swabs. Patients will independently apply the IMUs after receiving both verbal instructions and detailed written guidelines on proper attachment. Additionally, the positioning of the sensors does not affect the measurements, as the software used to analyze data from the OSK can account for variations in sensor placement.

Each participant will wear the IMU for two sets of three-day periods, during which time they will be instructed to remove them only in the shower or bath or at night. The following factors will be measured with the IMUs.

Daily distribution of standing, horizontal, and sitting position: Each position can be identified by the orientation of the proximal or distal IMU. Standing positions will be defined as positions in which the angle between the thigh and the transverse plane is more than 45° (α > 45°). A sitting position will be defined as a position in which the angle between the thigh and the transverse plane is less than 45° while the angle between the lower leg and the transverse plane is more than 30° (α < 45° and β > 30°). A lying position will be defined as a position in which the angle between the thigh and the transverse plane is less than 12° while the angle between the lower leg and the transverse plane is less than 30° (α < 12° and β < 30°).

Movement: A significant change in the angle of the knee and movement direction is defined as a change in the knee angle by 10°. 

Steps: Steps will be counted when a standing position is detected and a change in the angel of knee of more than 20° occurs. 

Movement over angular velocity: Measuring the angle of the knee at a sampling rate of 25 Hz allows us to calculate the angular velocity using the first-time derivative below.
(1)$$Angular\;velocity=\frac{change\;of\;knee\;angle\;}{time\;interval}\times tim$$

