## 3. Experimental Design

Over a three-day interval, occurring two weeks prior to a scheduled total knee arthroplasty, participants will be equipped with a wearable inertial movement unit (IMU). This device will facilitate the measurement of their performance-based knee function, utilizing parameters including steps taken per day, time taken to stand up, duration of active engagement, and rate of change in the knee angle. Additionally, PROMs (WOMAC and OKS) will be answered by the participants to obtain an initial measure of how they experience their own symptoms. As seen in Table 2, during the initial three-day period of wearing the inertial movement units (IMUs), the participants will also be asked to complete a Chair–Stand Up Test once a day. The data collected using the IMUs, the patient-reported outcome measures (PROMs) completed by the participants, and the results of the Chair–Stand Up Test will collectively serve to assess performance-based knee function. Preoperative leg-axis measurements will also be determined with the use of long leg X-rays. All total knee arthroplasties will be performed with kinematic alignment, utilizing an intramedullary femoral alignment and extramedullary tibial alignment. All patients will receive a cemented cruciate-retaining endoprosthesis, with a cemented posterior-stabilized (PS) tibial component, a cemented PS femoral component, and a fixed-bearing polyethylene inlay. In accordance with the guidelines established by the Institute for Quality Assurance and Transparency in Healthcare (IQTiG) for quality control, all patients will undergo physiotherapy during their hospital stay. The rehabilitation goals include sitting on the side of the bed, walking in the hospital corridors with crutches, ascending and descending stairs, and achieving knee flexion of 90 degrees. Three days post operation, knee alignment will be reassessed using long leg X-rays. At the six-week postoperative point, participants will undergo a second three-day period using IMUs to once again evaluate their performance-based knee function. During the second three-day period, participants will again perform the Chair–Stand Up Test once a day. Finally, participants will complete the two PROMs to provide a further subjective evaluation of their symptoms.

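### The three posture rules leave some reclined positions in no class and score lying with a well-bent knee as sitting; on unsigned angles it can also be scored as standing

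*Protocol article*

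**What the plan says.** Section 2.3 of the protocol article states that "Each position can be identified by the orientation of the proximal or distal IMU" and then fixes three rules:

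- Standing: "the angle between the thigh and the transverse plane is more than 45° (α > 45"°), with no condition on the lower leg.
- Sitting: "α < 45° and β > 30"°.
- Lying: "α < 12° and β < 30"°.

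No fourth class or default is named, and the text does not say whether the angles carry a sign. The step rule builds on the standing class: "Steps will be counted when a standing position is detected and a change in the angel of knee of more than 20° occurs".

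The sensors are worn in two three-day periods, and participants are told that "they will be instructed to remove them only in the shower or bath or at night". On accuracy, section 2.2 reports: "This testing revealed an average deviation of 5 degrees". Section 4 lists the posture distribution and steps among the sensor measures expected to improve after surgery. Section 3 names steps per day as a parameter of performance-based knee function.

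**The concern.** These are concrete thresholds for a named outcome, so they can be tested as written. Two problems appear.

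First, the rules do not cover all positions. The lying rule stops at α = 12°, but the sitting rule takes over above that only if β exceeds 30°. On unsigned angles, a leg raised on a pillow or a semi-reclined position can fall between the two.

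Second, the rules use only two leg segments, with no trunk condition. A person lying on the back with the foot on the bed and the knee bent has both segments tilted, as a sitting or standing person may have. On unsigned angles nothing separates a thigh that points up from one that points down.

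At stake is what the posture shares measure and, through the standing class, possibly the step count. If patients rest or exercise the knee differently two weeks before and six weeks after surgery, the classification error need not cancel in a pre-post comparison.

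**Working it through.** **Inputs.** The three posture rules and the step rule come from section 2.3. The sign of α and β is not stated. The plain reading of an angle between a segment and a plane is unsigned, 0° to 90°. The signed case (α negative when the knee is above the hip) is checked as an alternative. The plan gives no figure of its own to reproduce.

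**1. Coverage of the unsigned angle plane** (90 × 90 = 8100 square degrees)

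| Class | Region | Area | Share |
|---|---|---|---|
| Standing | α > 45° | 45 × 90 = 4050 | 50.0% |
| Sitting | α < 45°, β > 30° | 45 × 60 = 2700 | 33.3% |
| Lying | α < 12°, β < 30° | 12 × 30 = 360 | 4.4% |
| No class | 12° ≤ α ≤ 45°, β ≤ 30° | 33 × 30 = 990 | 12.2% |

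The rules do not overlap. Where α < 45° and β < 30°, (45 − 12)/45 = 73% of the thigh-angle range has no class. Examples of (α, β) without a class are (15°, 10°), (30°, 20°) and (40°, 25°).

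**2. Supine lying with the knee bent, unsigned angles.** Assume the heel is level with the hip and let R be the ratio of thigh to lower-leg length. Then sin β = R · sin α, and knee flexion = α + β. With R = 1, α = β = flexion/2, so:

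- α reaches 12° at 2 × 12 = 24° flexion, the end of lying;
- β reaches 30° at 2 × 30 = 60°, the start of sitting;
- α reaches 45° at 2 × 45 = 90°, the start of standing.

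Between 24° and 60° no class applies. For R from 0.9 to 1.2 (assumed range) the three cut points lie at 23–26°, 55–64° and 85–103°.

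**3. Steps.** A false step needs α > 45° while lying and a knee change of more than 20°. If the whole change must take place within the standing class, the knee has to sweep from 90° to beyond 90 + 20 = 110° (R = 1). The unclassified band adds no steps, because standing is not detected there.

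**4. Signed angles.** In supine bent-knee lying the knee is above the hip, so α is negative and below 12°. The position is then lying while β < 30°, which is up to about 60° flexion, and sitting beyond that. It is never standing, so the false-step route closes. The gap remains only where the knee is below the hip and the lower leg is near horizontal.

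**5. Time affected.** The document gives no time in any of these positions. As an illustration only, with an assumed 14-hour wear day, 0.25 to 3 hours in the gap would leave 0.25/14 = 1.8% to 3/14 = 21% of wear time unclassified.

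**The case against.** The strongest reply is that most of the problem depends on a sign convention that the article does not state. A 3-axis accelerometer can plausibly give segment direction relative to gravity. With signed angles, a raised leg with β below 30° is correctly lying, the 24–60° unclassified stretch disappears, and no false steps arise from supine lying. Sign handling and a default class may also sit in device documentation that is not shown. This stands as a limit on size. It does not remove the point: a knee-below-hip gap remains, and supine lying beyond about 60° flexion is scored as sitting under either convention. The article's remark that the software copes with variation concerns where the sensor is placed, not which class a position receives.

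Three stronger readings are tempting and not supported:

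- A reader might take 73% as lost time. It is a share of angle range within one sub-region. Sensors come off at night, which reduces the lying time at risk.
- A reader might conclude that the pre-post comparison is biased. The same rules apply to the same patients in both windows, and a differential shift is plausible but not shown. The primary hypothesis concerns prediction, not mean change in posture.
- A reader might cite the rehabilitation goal of "achieving knee flexion of 90 degrees" as evidence that patients will lie with deeply bent knees. It is a goal for the hospital stay and says nothing direct about the six-week window.

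It is also no defect in itself that the shares do not fill a 24-hour day, since the sensors are not worn throughout. Wear time is the right denominator.

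**Conclusion.** The point holds in a limited form. As written, the posture rules are not exhaustive: 12.2% of the unsigned angle plane has no class. Supine bent-knee lying receives different labels by flexion. With unsigned angles and equal segment lengths it is lying to about 24°, unclassified to about 60°, sitting to about 90° and standing above that. It is therefore wrong to say that bent-knee lying is always scored as sitting or standing.

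The standing label, the false steps and most of the gap rest on unsigned angles, which is the plain but unstated reading. The sitting label beyond about 60° does not depend on the sign. The posture distribution, and on unsigned angles the step count, may be misclassified. How much time is affected, and whether the error differs between windows, cannot be derived from the document.

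Measurement error adds a little. With β below 30°, a reading pushed upward across the 12° limit leaves every class instead of moving to a neighbouring one, and the stated average deviation is 5°. The point has no bearing on the sample size of 30.

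**What to change.** State the sign convention and use signed segment angles. Then:

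1. Standing: α > 45° with the knee below the hip.
2. Lying: α ≤ 45° with β ≤ 30°. Alternatively, report α from 12° to 45° with β ≤ 30° as a separate reclined class. Either choice closes the gap; step 3 deals with the bent-knee mislabelling.
3. Sitting: α ≤ 45° with β > 30°, with one exception. A raised thigh (knee above hip) is scored as lying or reclined only when the lower leg is not near vertical. Without that condition, sitting in a low chair would be scored as lying. The cut-offs for raised and for near vertical should be fixed in advance, with the stated 5° deviation in mind.
4. Count steps only in the corrected standing class.
5. Report each posture, and any unclassified remainder, as a share of wear time, and check that the shares sum to 100%.

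The cost is small: thresholds are reapplied to recorded angles, with no burden on participants. If the device software cannot be edited, the rules must be applied to the recorded angles outside it. Results become less comparable with any earlier work that used the present thresholds; reporting both sets once would show the difference. With two leg sensors and no trunk sensor, some ambiguity between deep bent-knee lying and low-chair sitting will remain and should be acknowledged.

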### 2.6. Chair–Stand up Test

The Chair–Stand Up Test is used to assess the ability to stand up from a chair at normal height and sit down again, without utilizing the arms [47]. The time it takes to complete 5 repetitions of standing up from a chair is recorded and serves to give an insight into the patients’ mobility [48]. The test is well established for assessing performance during TKA rehabilitation [49,50].

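### The step rule counts most sit–stand transfers as steps and misses steps with 20° or less of knee motion, so a pre/post step difference can partly reflect changed knee excursion

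*Protocol article*

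**What the plan says.** Section 2.3 of the protocol article gives the rule: "Steps will be counted when a standing position is detected and a change in the angel of knee of more than 20° occurs". The standing class that gates it depends on the thigh alone: "Standing positions will be defined as positions in which the angle between the thigh and the transverse plane is more than 45" degrees. Sitting is the class with "α < 45° and β > 30" degrees (α thigh, β lower leg). A person rising from a chair therefore passes from sitting to standing at α = 45°, halfway through the rise from a horizontal thigh. The rule has no condition on the lower leg, direction, duration or rhythm, and does not exclude transfers.

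The same knee-angle signal also drives the general movement parameter: "A significant change in the angle of the knee and movement direction is defined as a change in the knee angle by 10" degrees.

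The only accuracy figure is in Section 2.2: "This testing revealed an average deviation of 5 degrees". It concerns angles, and no check of step counts is reported. The Introduction says that "most patients with end stage osteoarthritis exhibit deficits in their ability to perform knee flexion", knee extension or both.

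Section 3 lists daily steps among the parameters of performance-based knee function. Section 4 expects a significant improvement in the sensor parameters, steps included. The Chair–Stand Up Test (Section 2.6: "The time it takes to complete 5 repetitions of standing up from a chair is recorded") is done once a day in both sensor windows (Section 3 and Table 2).

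**The concern.** A step count is meant to measure walking. This rule measures how often the knee moves through more than 20° while the thigh is above 45°. The two differ in two ways.

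- **False counts.** Standing up or sitting down moves the knee through a large angle, part of it within the standing class.
- **Missed counts.** A step taken with a stiff knee (20° or less of motion) is not counted. The protocol itself describes a population in which restricted knee motion is common.

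Missed steps matter more for the pre/post comparison. The operation is on the knee, so per-step excursion may differ between the two windows. The share of true steps counted would then differ too, and applying the same rule both times does not cancel this. Part of a change in knee motion would be reported as a change in walking. Because steps, movement and angular velocity all come from the knee-angle signal, some agreement among them is also built in.

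**Working it through.** The article states no step count, excursion or validation figure for this rule, so there is nothing of its own to reproduce. The check uses the published thresholds, plus assumptions labelled as such.

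**1. Does a sit–stand transfer meet the rule?**

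Inputs from Section 2.3: standing if α > 45°; a step if the knee change exceeds 20°.

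During a rise, knee flexion = 180° − α − β. Let β be the lower-leg angle when α crosses 45°, and e the flexion left when upright. The knee change inside the standing class is then

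(180° − 45° − β) − e = 135° − β − e.

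| β | e | Knee change while classed as standing | Over 20°? |
|---|---|---|---|
| 70° | 0° | 65° | yes |
| 90° (vertical) | 0° | 45° | yes |
| 90° | 20° | 25° | yes |
| 90° | 25° | 20° | no |
| 100° | 10° | 25° | yes |
| 100° | 15° | 20° | no |

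A transfer escapes only at e ≥ 25° with a vertical lower leg, or e ≥ 15° at β = 100°. This holds even if the whole 20° must occur inside the standing class.

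**2. How many false counts?**

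The chair test gives 5 rises + 5 sits = 10 a day, if the sensors are worn during it. Daily transfers and true steps are not in the article. Assume 40 to 120 transfers a day, one count each:

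- 6000 true steps a day: 40/6000 = 0.7% to 120/6000 = 2%.
- 1000 true steps a day: 40/1000 = 4% to 120/1000 = 12%.

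**3. What share of true steps is counted?**

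Assume per-step excursion is Normal(mean, SD). Share counted = P(excursion > 20°) = 1 − Φ((20 − mean)/SD).

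| Mean excursion | SD 5° | SD 10° |
|---|---|---|
| 25° | 0.841 | 0.691 |
| 30° | 0.977 | 0.841 |
| 35° | 0.999 | 0.933 |
| 45° | 1.000 | 0.994 |
| 50° | 1.000 | 0.999 |

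**4. What does that do to a pre/post difference when walking is unchanged?**

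Apparent change = share after / share before − 1.

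| Shift in mean excursion | SD 5° | SD 10° |
|---|---|---|
| 25° to 35° | 0.999/0.841 − 1 = +19% | 0.933/0.691 − 1 = +35% |
| 30° to 25° | 0.841/0.977 − 1 = −14% | 0.691/0.841 − 1 = −18% |
| 35° to 45° | +0.1% | +6.5% |
| 45° to 50° | 0.0% | +0.5% |

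**5. How sensitive is the count to the threshold?**

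If the stated 5° deviation moved the effective threshold to 15° or 25°, the share counted at mean 25° and SD 5° would be 0.977 or 0.500. This is an upper view: a constant angle offset cancels in a change of angle, so the 5° need not carry over in full.

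**The case against.** The strongest reply is about size. The article gives no per-step excursion. The Introduction speaks of deficits in the ability to flex or extend, which is not the same as excursion during walking. If typical excursion is about 45° or more, nearly all steps are counted and the bias all but disappears. This stands: the documents are compatible with anything from about zero to the 35% in the table, and 35% depends on one chosen SD and one chosen shift.

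The transfer error is small against daily steps for an active patient. The chair-test counts occur in both windows and largely cancel in the pre/post difference. That also stands.

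Three stronger readings are tempting but not supported.

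- A reader might infer that every transfer is counted. The geometry says most: a patient who keeps enough flexion when upright escapes, and extension deficits are part of this population.
- A reader might infer that the count measures knee excursion instead of walking. At an assumed mean of 30° or more, the calculation still captures 84% or more of true steps.
- A reader might infer that the primary prediction hypothesis is undermined. The calculation concerns a shift in means, not the pre/post association, and steps are one of several parameters and are not named as the primary one.

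Finally, the device software may apply filters that a condensed article omits. That is possible. But the article gives an operational definition with explicit thresholds, and as printed it contains no such filter. If filters exist, the definition should say so.

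**Conclusion.** The point holds in limited form. From the published thresholds alone, most sit–stand transfers qualify as steps and every step with 20° or less of knee motion is lost. The pre/post step difference can therefore partly reflect a change in knee excursion. The bias follows the direction in which excursion changes, and the article does not give that direction.

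The size is uncertain and rests on the assumed normal distribution, means and SDs. It is material if typical excursion lies around 20–35° (19–35% for a shift from 25° to 35°) and 0.5% or less above about 45°. Transfer inflation is certain in direction but modest: 0.7–2% at an assumed 6000 steps a day and 4–12% at 1000. Differential under-counting is the more serious part. The miscount affects a named outcome and can be reduced at small cost, so it should be corrected before the step data are analysed.

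**What to change.** 1. Do not count as a step any knee-angle change that accompanies a change between the sitting and standing classes, or that occurs during the Chair–Stand Up Test. The posture classes already recorded are enough for the first; the second needs the test times marked.
2. Report the step count at alternative knee thresholds, for example 15° and 25° (20° ± the stated 5° sensor deviation), alongside 20°.
3. Where raw signals are kept, add a count from a cycle-based lower-leg detector as a sensitivity analysis. It should not replace the main count: nothing in the article shows that it performs better here, and requiring several cycles could drop short indoor walks.
4. Present any pre/post step change together with the change in per-step knee excursion, and interpret the two jointly.
5. If the device software already filters transfers, state this in the definition.

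The cost is modest reprocessing, with no extra visits or patient burden. A genuine step taken immediately at a transition may be dropped. Items 2 and 3 depend on the stored signals being retained: Section 2.2 says that data can be stored on the device, not that they will be kept.
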